#### Statistical analysis

A series of 3 (condition: control, intervention, and intervention with text message) × 2 (time: 6 and 12 weeks) mixed model multivariate analyses of covariance (MANCOVAs) with time as a repeated measures variable will be used examine the effects of the intention over time on study outcome variables. Baseline measures will be covariates in the model. A separate MANCOVA will be conducted for each set of dependent outcome variables: biomedical, behavioural and psychological. Pending significant multivariate effects, follow-up univariate analysis of covariance (ANCOVAs) will be used to identify differences for individual variables within each outcome set. Post-hoc follow-up tests will also be conducted to locate individual differences at the time intervals. Mediation analyses will be conducted by mediated multiple linear regression analysis with dummy-coded intervention conditions as the independent predictor variables, the constructs from the HAPA included as mediating variables, and the primary and secondary biomedical outcome variables as the dependent variables. Mediation will be confirmed through significant bootstrapped indirect effects using Preacher and Hayes’ [56] algorithms for multiple mediation and the PROCESS macro. Missing data will be handled by multiple imputation using regression analysis with the Markov-chain Monte Carlo (MCMC) estimation method. In addition, we will adopt a full intention-to-treat analysis with last measured data points carried forward in order to provide a conservative estimate of the effects.

Sample size has been determined by a power analysis using the G*Power 3.1 Program, suitable to evaluate differences between the three condition levels greater than 10%, with statistical power set at > 0.80 and alpha set at *p* < .05 [57]. A large effect size is assumed as previous studies that have used implementation intentions and reminder text messages [31], as well as studies using mental imagery and implementation intentions to increase exercise behaviour [58], have found large effect sizes. Given the estimated effect size, the total sample size required post-test is 66 and considering a potential 35% drop out rate and eliminations of cases due to missing data or spoilt questionnaires based on previous trials [21], we plan to recruit 102 participants at baseline or until the required sample size has been achieved.

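### The intention-to-treat analysis is tied to last observation carried forward on the ground that it is conservative, which is not so by construction, and neither it nor multiple imputation is named as the main analysis

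*Protocol article*

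**What the plan says.** All three relevant statements stand in the Statistical analysis section of the protocol article.

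- On missing data generally: "Missing data will be handled by multiple imputation using regression analysis with the Markov-chain Monte Carlo (MCMC) estimation method".
- Directly after that, introduced as an addition: "we will adopt a full intention-to-treat analysis with last measured data points carried forward in order to provide a conservative estimate".
- In the sample-size paragraph: "the total sample size required post-test is 66", and then, "considering a potential 35% drop out rate and eliminations of cases due to missing data or spoilt questionnaires based on previous trials", "we plan to recruit 102 participants at baseline or until the required sample size has been achieved".

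The label intention-to-treat is attached only to the carried-forward analysis. Neither that analysis nor the imputation is called main, primary or supporting.

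Three other sections bear on the point. The section on diet, physical activity and weight loss cites a loss of about 0.5 kg a week for a 500-calorie daily reduction. The section on weight-loss information for all participants says that every arm gets the same diet and activity guidance. The Discussion accepts that the more motivated may be the ones who stay.

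**The concern.** The justification given for LOCF is a positive statement about its behaviour, and as a general property it is wrong.

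When weight is falling in all arms, a value carried from baseline or week 6 omits the change that would have followed. Each dropout's recorded loss is therefore too small. If one arm has more dropouts, or earlier ones, its mean is pulled further towards no change, and a difference between arms appears that treatment did not cause. The direction depends on which arm loses more people. LOCF also enters each carried value as if it had been measured, so the standard error takes no account of the uncertainty about the missing value.

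Two things are at stake. The analysis labelled intention-to-treat could show a weight difference that is not there, or hide one that is. And with two analyses and no stated order between them, the more favourable could be put forward once results are known.

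**Working it through.** **1. The plan's own figures.** The article assumes a large effect but gives no number. I take Cohen's f = 0.40, three equal groups, alpha 0.05 and the omnibus F test. Power is 0.805 at N = 64 and 0.818 at N = 66, the first balanced total above 0.80 (22 per arm). With 35% loss, 66 / 0.65 = 101.5, rounded up to 102. Both stated figures reproduce. The 66 are those left after dropout and eliminated cases. An imputation or a full intention-to-treat analysis would use all 102, or 34 per arm if allocation is equal (the ratio is not stated).

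**2. Formula for the LOCF bias with no true effect.** Let all arms share a mean loss of L6 at week 6 and L12 at week 12, and let half of the dropouts leave before week 6.

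- A participant who leaves before week 6 is carried from baseline, so L12 is missing from the record.
- A participant who leaves after week 6 is carried from week 6, so L12 − L6 is missing.
- False difference = (difference in dropout) × [0.5 × L12 + 0.5 × (L12 − L6)].

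**3. A moderate scenario.** Assumed, not in the article: L6 = 2.5 kg, L12 = 4 kg, SDs of 2.5 and 4 kg, and dropout at random within arm. The bracket is 0.5 × 4 + 0.5 × 1.5 = 2.75 kg.

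- 25% v 45%: means 0.75(−4) + 0.125(−2.5) = −3.31 and 0.55(−4) + 0.225(−2.5) = −2.76. The difference is 0.20 × 2.75 = 0.55 kg.
- 20% v 50%: 0.30 × 2.75 = 0.83 kg.
- 45/30/30 or 25/40/40: 0.15 × 2.75 = 0.41 kg between the odd arm and the others.

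Simulated rejection rates at a nominal 5%, 34 per arm, week-12 change, 20,000 runs, with a week 6 to 12 correlation of 0.7 or 0.8:

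| Dropout | Test | Type I error |
|---|---|---|
| 35 / 35 | two arms | about 5% |
| 30 / 40 | two arms | about 6% |
| 25 / 45 | two arms | about 9.5% |
| 45 / 25 | two arms | about 9.5%, sign reversed |
| 20 / 50 | two arms | about 15% |
| 35 / 35 / 35 | three-arm F | about 5% |
| 45 / 30 / 30 | three-arm F | about 7% |
| 25 / 40 / 40 | three-arm F | about 7% |

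**4. The upper end.** At the article's cited 0.5 kg a week, fully achieved, L6 = 3 kg and L12 = 6 kg. Each 10-point excess of dropout then gives 0.10 × 3 = 0.3 kg if participants leave after week 6, or 0.10 × 6 = 0.6 kg if they leave before it. With an assumed SD of 4 kg, a week-12 ANCOVA on three arms of 34 (2,000 runs per scenario) gave:

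- control 45%, interventions 30% each: false benefit of 0.7 to 0.9 kg, type I error 10 to 15%;
- control 25%, interventions 40% each: false harm of 0.7 to 0.9 kg, type I error about 9 to 13%;
- 35% in each arm: no bias, type I error 4.1 to 4.6%.

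Complete-case analysis stayed near 5% throughout, because dropout was simulated as random within arm. That says nothing about informative dropout.

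**5. Equal loss with a true effect.** With 35% loss in every arm, a 6 kg common loss, SD 4 kg and a true benefit of 2 kg, LOCF estimated 1.3 to 1.45 kg. This dilution is the one case examined in which the article's description fits.

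**The case against.** Several stronger readings are tempting, and the article does not support them.

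- **Three conflicting rules.** A reader might infer that imputation, LOCF and case elimination contradict one another. LOCF is introduced as an addition, so it reads naturally as a second analysis beside imputation. The phrase "35% drop out rate and eliminations of cases due to missing data or spoilt questionnaires" belongs to a recruitment allowance and is not an analysis rule. What remains is that no analysis is named as main, and that the allowance does not match an analysis of all 102.
- **35% loss creates an effect.** It does not. With equal loss, type I error stays at about 5%. The 35% also combines dropout with eliminated cases, so it is not a dropout rate. Unequal loss is needed, and the article gives no loss by arm.
- **Unequal loss is likely and would favour the intervention.** The Procedure section gives baseline sessions of 90 to 120 for control and 150 to 210 for the intervention arms, and only one arm receives texts. That makes unequal loss plausible, no more. The video is viewed once, with breaks allowed. The longer version goes to both intervention arms, so loss driven by burden would bias against them, and burden cannot separate the two. Only text contact could push towards a false benefit for the text arm, and no retention effect is documented.
- **A week-6 loss is frozen before regain.** No figure in the article supports regain within 12 weeks. The calculation here assumes continued loss.

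It is also fair to say that ranking main and supporting analyses is often left to a statistical analysis plan, which is not at hand. That weakens the complaint about the unnamed main analysis. It does not rescue the stated justification, which such a plan would have to contradict.

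**Conclusion.** The point holds in a limited form. The article attaches intention-to-treat to LOCF and gives a reason that is not generally true. LOCF can produce a false benefit or a false harm when the amount or timing of loss differs between arms, and with equal loss it dilutes a true effect.

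The sizes above rest on assumed common weight loss, SDs, dropout by arm, timing and within-arm randomness of dropout. The simulated tests are simpler than the planned repeated-measures MANCOVA. They show that the error can be material. They do not predict it for this trial. I rate this as should-fix: the planned imputation already offers a sound main analysis, and the repair is mostly wording.

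**What to change.** - Name one main intention-to-treat analysis of all randomised participants: the multiple imputation already planned, done by arm and including baseline and week-6 weight, or a likelihood-based mixed model.
- Delete the claim that LOCF is conservative. Drop LOCF, or keep it only as a labelled sensitivity analysis.
- Add a sensitivity analysis that shifts the imputed values by arm and reports how far they must move before the conclusion changes.
- State that incomplete cases are not eliminated from the main analysis. The 35% can stay as a recruitment allowance.

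The cost is a few sentences, a little more programming, and standard errors somewhat wider than under LOCF. The figures 66 and 102 stand.

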## Discussion

The purpose of the current intervention is to examine the effectiveness of an intervention using implementation intentions and mental imagery strategies aimed to promote adherence to diet and physical activity guidelines to assist obese or overweight individuals in achieving weight loss. The intervention will also evaluate whether mobile phone goal reminder text messages will be effective in augmenting the intervention effectiveness. The randomised control trial will consist of participants being randomly allocated to one of three conditions: (1) a psycho-education plus an implementation intentions and mental imagery condition; (2) a psycho-education plus an implementation intentions and mental imagery condition with text messages; or (3) a psycho-education control condition. The intervention will be delivered via video presentation, an approach that will increase the intervention’s applicability in multiple contexts and keep costs low. The research will be guided by the theoretical framework offered by the HAPA to explain the effects of the intervention components and the mechanisms and mediators involved. The key behavioural outcomes will be adherence to a calorie restricted diet and participation in 30 minutes of daily physical activity measured at 6 and 12 weeks post-intervention. The intervention will also explore changes in additional key biomedical (for e.g., body fat, and waist-hip circumference), psychological (for e.g., quality of life, motivation, and planning), and behavioural (for e.g., self-reported diet intake and physical activity involvement) health-related outcomes.

A large number of questionnaires and assessments completed by participants may have the potential to introduce considerable response burden on participants and lead to increased measurement error and affirmation bias. Furthermore, it is possible that only motivated and potentially compliant people will be likely to persist with the study introducing bias to the eventual findings. As with all research the number of measurements selected is a trade-off between collecting adequate data to evaluate the effectiveness of the intervention relative to participant burden and demand. However, it must be stressed that we have put a number of strategies in place to manage the issue of participant burden and allay associated confounding effects. Specifically, during the video intervention manipulation participants will be encouraged to take as many breaks as needed and have the opportunity to pause the video at their own volition. In addition, following the first appointment most of the measures and assessments will only be completed relatively infrequently i.e. at six-week intervals.

A unique aspect of the present study is the adoption of two key theory-based intervention techniques, implementation intentions and mental imagery, in synergy to assist participants in achieving their weight loss goals. The inclusion of these components together is consistent with contemporary theory based on the HAPA that two phases to action exist and the current intervention aims to induce behavioural engagement through the inclusion of components targeting both phases. The theory-related components and concepts outlined in the current protocol are explicitly linked using a systematic intervention-matching procedure providing other researchers with a precise account of the intervention content and its theoretical basis. The current research is also unique as it will examine whether augmenting the intervention using text messages by mobile phone will enhance the effectiveness of the intervention messages. Prestwich and colleagues [31] paired implementation intentions with text message goal reminders to achieve participant weight-loss and participation in physical activity the current study extends this research by including the motivational intervention component of mental imagery alongside implementation intentions with text messages.

Another unique component of the current intervention is the adoption of a streamlined and efficient study design with low administration and personnel required with intervention delivery being via video presentation. The significance of implementing a theory based intervention via video presentation means that the intervention is evidence based, cost effective, requires minimal contact with the participant, provides flexibility for delivery, and is easily available. The intervention may provide health professionals with a means of assisting obese or overweight individuals that seek weight-loss assistance; through providing patients with a copy of the evidence based self-help approach reliance on health professionals may be reduced, saving time and costs for both the consumer and the health professional. In addition, individuals would have the flexibility to access the intervention program at a time of their own convenience, and to view the presentation using multiple devices such as a computer and laptop.

## Appendix A: complete list of inclusion and exclusion criteria

### Inclusion criteria

Participants must be between the age of 18 to 65 years old, and overweight or obese (Body Mass Index between: 25 to 40). The individual must not have been involved in any other weight loss studies in the last 6 months, and will need the ability to restrict dietary intake, and increase physical activity levels. A reliable mobile phone with text messaging ability features is needed. The participant is required to attend the Clinic in Perth and attend all data collection time periods. Participants will be expected to complete the questionnaires and a record of physical activity and food intake for a 3 day periods when required. Participants will need to consent to blood samples, and the DEXA body composition scan.

### Exclusion criteria

Females who are pregnant, trying to become pregnant, or lactating will be excluded from the study. Participants who are diagnosed or believe they may have severe depression, eating disorders (bulimia or binge eating), health issues, and/or major illnesses/diseases will also be excluded. Major illnesses/diseases in the context of the present study includes any disease, illness, or chronic condition that may inhibit or negatively impact on participants’ ability to safety engage in a minimal contact/support intervention, or engage in a low calorie diet and physical activity intervention. Example conditions are: diabetes, heart disease, cancer, or some mental health conditions that would inhibit the participant’s health or ability to engage in the program safely with minimal support and supervision. Participants on anti-depressant medication may be excluded. In addition, any individual with past major operations in the last 2 years, or with any upcoming major operations, or cardiovascular events in the last 6 months will be excluded. Participants who consume opioids or regularly have more than two alcoholic drinks per day will also be excluded.

## Abbreviations

ANOVAS: Analysis of covariance
ANZCTR: Australian New Zealand Clinical Trial Registry
BMI: Body mass index
BMR: basal metabolic rate
DASS-21: Depression anxiety stress scales-21
DBP: Diastolic blood pressure
DEXA: Dual-energy X-ray absorptiometry
HAPA: Health action process approach
HEALTHI: Healthy eating and active lifestyle health intervention
HDL: High-density lipoprotein
IPAQ: International physical activity questionnaire
IWQOL-Lite: The impact of weight on quality of life questionnaire
LDL: Low-density lipoprotein
MANCOVA: Mixed model multivariate analyses of covariance
SBP: Systolic blood pressure
TFEQ-R18: Three factor eating questionnaire
TG: Triglycerides
